## Aims and hypotheses

To address this evidence gap, the primary aim (Aim 1) of the PRO-ACTIVE trial is to compare the effectiveness of PRO-ACTIVE versus RE-ACTIVE swallowing interventions among patients with HNC planned to undergo RT. We hypothesize that at 12-months post radiotherapy the combined PRO-ACTIVE therapies are more effective than RE-ACTIVE therapy (Hyp 1.1); and, if so, that more intensive PRO-ACTIVE (EAT + EXERCISE) is superior to less intensive PRO-ACTIVE (EAT) (Hyp 1.2). Effectiveness will be measured based on reduced duration of feeding tube dependency, a pragmatic outcome valued by diverse stakeholders including patients, caregivers and clinicians [13, 21, 25, 26].

The second aim (Aim 2) of the PRO-ACTIVE trial is to compare the relative benefit or harm of PRO-ACTIVE to RE-ACTIVE swallowing intervention on all secondary outcomes at both 3- and 12- months post radiotherapy, namely: swallowing impairment, maximum interincisal opening (trismus), swallowing-related QOL, symptom burden, self-reported pneumonia, malnutrition and mood disorder, cancer coping strategies, diet level, feeding tube rates, weight loss, hospitalization and/or emergency department (ED) presentation. In addition, the second aim will compare the benefit on reduced duration of feeding tube presence at 3-month post radiotherapy. Our hypothesis for this second aim is that the combined PRO-ACTIVE interventions will result in better secondary outcomes at 3- and 12- months following the completion of RT (Hyp 2.1). As in our primary aim, for each secondary outcome for which PRO-ACTIVE is superior, dose response of the PRO-ACTIVE arms will be examined hypothesizing the more intensive therapy as superior (Hyp 2.2).

The third aim (Aim 3) of the PRO-ACTIVE trial is to explore the relative benefit or harm of the PRO-ACTIVE and RE-ACTIVE swallowing interventions in relevant subgroups according to the following: age, tumor site, prior surgery, radiation dose, chemotherapy use, and prophylactic feeding tube use. Our hypothesis for this third aim is that all interventions will be more effective in the following higher risk subgroups: older age; non-HPV related cancer sites; prior surgery; higher radiation dose; chemotherapy (yes); and, prophylactic feeding tube insertion (yes).

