The randomization of participants will be stratified by participating site using a centralized, automated and concealed process conducted by the Data Coordinating Center (DCC). Participants and therapy providers will not be blinded; however, clinical raters and data analysts will be blinded to the study arm to minimize bias. Eligible patients will be randomized in a 1:2:2 allocation to RE-ACTIVE (Arm 1, *n* = 190) and each of the PRO-ACTIVE arms (Arms 2 and 3, *n* = 381 per group). All patients will be followed to 12 months post-RT. The main intention to treat analysis will compare duration of feeding tube dependence post-RT. The study schemata is shown in Fig. 1.

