#### Secondary endpoints

The analysis of the secondary endpoints is not dependent on the findings of the primary endpoint. The hypothesis (Hyp 2.1) is that the combined PRO-ACTIVE interventions will result in a better secondary outcomes including videofluoroscopic swallowing evaluations, functional status measures, health status measures, and patient reported outcomes 3 months following the completion of RT. For the secondary outcomes, ITT analysis will again use a gate-keeper approach to assess differences between arms. Continuous outcomes will be evaluated with ANCOVA approach (multiple linear models regressing outcome on randomization arm plus the baseline measure for adjustment) at the 3-month post-treatment interval when a baseline measurement is present and a t-test (or suitable replacement) otherwise. The treatment effect will be expressed as the mean adjusted difference, or equivalently, mean adjusted change along with 95% confidence intervals. Binary outcomes will be compared by means of a chi-square test or Fisher’s exact test if expected counts are less than 5 and treatment effects will be expressed as risk differences with 95% confidence intervals. Sensitivity will be assessed in terms of consistency of inference as well as magnitudes of effect size using distributional measures of Minimal Clinically Important Difference (MCID) [67] or anchor-based MCID [44] when available to interpret whether observed differences are meaningful. Exploratory analyses will be conducted on all outcomes with repeated measurements using mixed-effect models to examine time by treatment interactions. Exploratory subgroup analyses will examine the relative benefit or harm of the PRO-ACTIVE and RE-ACTIVE swallowing interventions in relevant subgroups according to the following: patient (age, tumor site, prior surgery); and provider (radiation dose, chemotherapy use, prophylactic feeding tube use).

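### Hyp 2.1 is set at 3 and 12 months in the aims but at 3 months in the analysis section, so no non-exploratory 12-month test is named for continuous secondary outcomes; separately, the secondary analyses omit site

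*Protocol article*

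**What the plan says.** All places are in the protocol article.

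- **Aims and hypotheses.** Aim 2 compares PRO-ACTIVE with RE-ACTIVE "on all secondary outcomes at both 3- and 12- months post radiotherapy". Hyp 2.1 is that the combined PRO-ACTIVE arms "will result in better secondary outcomes at 3- and 12- months following the completion of RT (Hyp 2.1"). Hyp 2.2, the comparison of the two PRO-ACTIVE intensities, is examined for each secondary outcome on which PRO-ACTIVE is superior.
- **Secondary endpoints (Statistical analysis).** The same Hyp 2.1 is restated for a list of outcomes ending in "patient reported outcomes 3 months following the completion of RT". Continuous outcomes with a baseline value are analysed by ANCOVA, described as "multiple linear models regressing outcome on randomization arm plus the baseline measure for adjustment) at the 3-month post-treatment interval"; those without a baseline get a t-test or a suitable replacement. For the rest, "Binary outcomes will be compared by means of a chi-square test" (Fisher's exact test if expected counts are small), with no visit named. Finally, "Exploratory analyses will be conducted on all outcomes with repeated measurements using mixed-effect models to examine time by treatment interactions".
- **Overview of trial design.** "The randomization of participants will be stratified by participating site".
- **Primary endpoint (Statistical analysis).** The primary regression includes facility as a categorical covariate, to allow for practice variation across the eleven sites. No secondary analysis mentions site.
- **Outcome measures and Table 1.** Patients are followed to 12 months to examine long-term effectiveness. Videofluoroscopy, trismus, PSS-HN, MDADI, MDASI-HN, the coping inventory and EQ-5D-5L are all scheduled at 12 months.

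**The concern.** One numbered hypothesis carries two different sets of time points. If the aims govern, half of Hyp 2.1 has no named primary-style analysis for the continuous outcomes. If the analysis section governs, the aims promise a comparison that the plan does not make. Hyp 2.2 inherits the problem: its gate opens on a Hyp 2.1 result, and for continuous outcomes no such result is defined at 12 months.

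The practical risk is discretion. With two visits in the hypothesis, one in the ANCOVA and none in the binary tests, the visit that counts could be settled after the data are seen. If both visits were tested at 0.05 with no rule, the error rate per outcome would rise.

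The site omission is a separate and smaller matter. A stratified randomization balances the arms within site. An analysis that ignores site leaves between-site variation in the standard error, although the design has already removed it from the comparison.

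**Working it through.** **1. Time points side by side.**

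| Item | Aims and hypotheses | Secondary endpoints |
|---|---|---|
| Hyp 2.1 | 3 and 12 months | 3 months |
| Continuous outcomes with a baseline | 3 and 12 months | ANCOVA at 3 months |
| Continuous outcomes without a baseline | 3 and 12 months | t-test; visit not clearly stated |
| Binary outcomes | 3 and 12 months | chi-square or Fisher; no visit stated |
| Longitudinal model | not mentioned | exploratory, time-by-treatment interaction |

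The mixed models would use the 12-month data. However, a time-by-treatment interaction asks whether the arm difference changes between visits. It is not the between-arm difference at 12 months, and it is not placed in the gate-keeper.

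**2. The article's own Aim 2 figure (Sample size calculation).** Stated: 0.24 SD for Arm 2 versus Arm 3, 80% power, two-sided 0.05, 26% attrition.

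- Patients per arm: 381 × 0.74 = 282.
- Detectable difference: (1.960 + 0.842) × √(2/282) = 0.236 SD; power at 0.24 SD is 81.3%. The figure reproduces.
- The n = 361 per group printed beside it is the 5%-attrition number and would give 89.7% power. That mismatch is a separate matter and does not affect this point.

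**3. Hyp 2.1 at the same effect size.** The article gives no power for this comparison; using 0.24 SD here is my choice.

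- Patients: 190 × 0.74 = 141 and 762 × 0.74 = 564.
- z = 0.24 / √(1/141 + 1/564) = 0.24 / 0.0942 = 2.55.
- Power with no between-site variance: Φ(2.55 − 1.96) = 72.2%.

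**4. Effect of leaving out site.** Let R² be the share of outcome variance explained by site. The article gives no value, so 5-10% is an assumption. With arms balanced within site, the true variance of the difference is (1 − R²) times what the unadjusted test uses.

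- Actual alpha, unadjusted = 2 × [1 − Φ(1.96/√(1 − R²))]
- Power, unadjusted = Φ((2.55 − 1.96)/√(1 − R²))
- Power, site in the model = Φ(2.55/√(1 − R²) − 1.96)

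| R² | Actual alpha | Power without site | Power with site | Gain |
|---|---|---|---|---|
| 5% | 0.044 | 72.7% | 74.4% | 1.7 points |
| 10% | 0.039 | 73.3% | 76.6% | 3.3 points |

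At R² of 1% or 2%, actual alpha is 0.049 or 0.048, so the effect is trivial. These are normal approximations and ignore the precision gained from the baseline covariate.

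**5. Testing both visits without a rule.** Two tests at 0.05 per outcome give 1 − 0.95² = 9.75% if independent. Repeated measurements on the same patients are likely to be positively correlated, which makes the true figure lower.

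**The case against.** Several stronger readings are tempting, and the article does not support them.

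- **That the 12-month secondary data have no planned analysis, or that only 3 months is tested.** The mixed models cover every outcome with repeated measurements, and the binary tests carry no restriction to 3 months. What is missing is narrower: a non-exploratory 12-month between-arm test for continuous outcomes.
- **That the trial forfeits a confirmatory 12-month result.** The article does not give the secondary outcomes confirmatory standing. They are analysed regardless of the primary result, the gate works within each outcome, and no error control across outcomes is stated even at 3 months. The 12-month horizon of the primary endpoint belongs to feeding tube duration.
- **That omitting site causes the 12-month gap or risks false positives.** The two points are unrelated, and the omission makes the tests conservative.

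It can also be said that a separate analysis plan may specify the 12-month tests, that nothing obliges secondary models to match the primary one, and that the baseline covariate may already absorb part of any site difference. The last two keep the site point small. The first does not remove the main point: an article may leave detail to a fuller document, but here it states one hypothesis in two incompatible ways.

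**Conclusion.** The point holds in limited form. The aims and the analysis section disagree on when Hyp 2.1 is tested. As written, continuous secondary outcomes have no non-exploratory 12-month between-arm test and therefore no Hyp 2.2 gate at 12 months, and the visit for binary outcomes is left open. This rests on the text alone and needs no assumption.

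The site omission is a secondary inefficiency. Its size depends on the assumed 5-10% of variance and on applying 0.24 SD to Hyp 2.1: alpha slightly below nominal and about 2 to 3 points of power. Neither point touches the primary endpoint. Both are worth correcting before unblinded analysis, because a visit chosen afterwards would weaken whatever is reported.

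**What to change.** Reconcile Aims and hypotheses with Secondary endpoints in one of two ways.

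1. **Keep both visits.** Run the same ANCOVA at 12 months, or a mixed model reporting the 3- and 12-month arm contrasts. State the visits for binary outcomes and for outcomes without a baseline. Within each outcome, put the visits in a fixed order or split alpha between them, and say where the Hyp 2.2 tests stand in that scheme.
2. **Limit Hyp 2.1 and 2.2 to 3 months** in the aims, name 3 months for the binary tests, and label 12-month secondary results exploratory.

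In either case, add site to the continuous secondary models. For binary outcomes, use a site-stratified Mantel-Haenszel risk difference with a Cochran-Mantel-Haenszel test. Other stratified methods would also serve.

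Cost: wording and minor extra analysis work. No patients or visits are added. Under option 1, sharing alpha has a price. With an equal split, each visit is tested at 0.025 (critical value 2.24), and power for Hyp 2.1 at 0.24 SD falls from 72% to Φ(2.55 − 2.24), about 62%, before any gain from baseline or site. A fixed order keeps 0.05 at each step, but the second visit is tested only if the first succeeds.

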#### Secondary outcomes

Secondary outcome measures represent both clinician-graded and patient reported outcome (PROs) measures. These measures were selected based on feasibility [38] at all sites, psychometric validation, familiarity to the investigative team, and/or wide used in routine settings of care, thereby maintaining pragmatic standards. The secondary outcomes are the following:
The MD Anderson Dysphagia Inventory (MDADI)

MDADI is a widely used PRO instrument to evaluate swallowing-related QOL in HNC patients [39]. The 20-item questionnaire quantifies an individual’s global, physical, emotional, and functional perceptions of swallowing ability. MDADI was internally developed and validated at MD Anderson Cancer Center and has been integrated in the MDACC dysphagia clinic for more than 10 years. Questionnaire development included engagement of providers and patients with HNC who experienced dysphagia iteratively throughout conception and refinement of the final scale. In a validation sample of 100 patients with HNC, concurrent validity was moderate by comparison with the Performance Status Scale-Head and Neck (Spearman correlation, 0.47-0.61). Correlation with the subscales of SF-36 demonstrated convergent and divergent validity of the MDADI. Test-retest reliability (physical, 0.86; emotional, 0.88; functional, 0.88) and internal consistency reliability (overall Cronbach’s alpha, 0.96) were sound [39]. Subsequent validation studies further demonstrated suitable psychometric properties in patients with different ethnic-cultural backgrounds [40–42]. Perceived dysphagia as quantified by the MDADI is time-dependent, radiotherapy dose-dependent and varies by extent of surgery and tumor site in HNC samples [35, 43]. The investigators have previously shown a 10-point between-group difference to discriminate a clinically meaningful difference in swallowing outcome [44].
2)The MD Anderson Symptom Inventory for Head and Neck Cancer (MDASI-HN)

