### Statistical analysis

#### Primary endpoint

For the primary endpoint, an intention-to-treat (ITT) approach will be applied incorporating a gate-keeper method to control risk of Type 1 error in the setting of multiple comparisons [64, 65]. The primary hypothesis (Hyp 1.1) is that the combined PRO-ACTIVE interventions (PRO-ACTIVE EAT and PRO-ACTIVE EAT+EXERCISE) will result in a better swallow outcome compared to RE-ACTIVE as measured by duration of feeding tube use in the first year after the completion of RT. If PRO-ACTIVE is superior in Hyp 1.1, we will assess the dose response of the PRO-ACTIVE arms. The secondary hypothesis (Hyp 1.2) is that the most intensive intervention (PRO-ACTIVE EAT+EXERCISE) will be more effective than the least intensive (PRO-ACTIVE EAT).

The initial analysis will compare the RE-ACTIVE group to the combined PRO-ACTIVE groups in terms of the duration of feeding tube use operationalized as count of days of tube use from end of RT to last tube use within the 12-month study period by means of a multiple linear regression model with covariate adjustment. The presence of a feeding tube which is not being used for feeds is disregarded. The treatment effect will be expressed as absolute mean difference along with 95% confidence intervals. If this test yields *p* < 0.05, the two PRO-ACTIVE groups (EAT versus EAT+EXERCISE) will be compared using the same linear analysis method. The meaningful variables we will include in the regression model are: age (as a continuous variable); HPV status (oropharyngeal site vs all others); surgery (yes/no); chemotherapy (yes/no); radiation dose (as a continuous variable); and, facility (as a categorical variable to account for practice variation across the eleven sites).

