#### Sub-group analyses (heterogeneous treatment effects, HTEs)

Acknowledging that certain groups may benefit substantially while others may benefit far less, exploratory heterogeneous treatment effect (HTE) analyses are planned (Aim 3). The goal of the HTE analyses is to explore if there are subgroups for whom swallowing interventions have varied impact. For hypothesis-generating analyses, HTEs will be assessed by testing the treatment arm by subgroup interaction. Analyses are planned according to two potential sources of HTE [34]: the patient and provider**.** For parsimony, a likelihood ratio test will examine proposed HTEs simultaneously. Irrespective of their significance, the subgroup effects will be reported (with 95% confidence intervals) to be assessed in terms of clinical significance.

We have identified several participant subgroups for whom differences in treatment response or swallowing outcomes may exist. Preliminary data suggest superior swallowing outcomes in younger patients [10], those with HPV-associated cancers [68–70] those with no prior surgery [68], those who receive lower doses of RT [10], those who avoid chemotherapy [68, 71] and who avoid prophylactic feeding tube placement [9]. Each of these classifications will be examined as relevant subgroups in the exploratory HTE analysis, as justified below:

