### Sample size calculation

Sample size calculations, based on a 2-sample t-test, assume 952 patients enrolled with 1:4 allocation to RE-ACTIVE (Arm 1, *n* = 190) and PRO-ACTIVE arms (Arms 2 and 3, *n* = 381 per group). The attrition factor is set at 5% because the primary endpoint can be ascertained without clinical encounter. Thus, the resultant sample size estimated is 180 in Arm 1, 361 in Arm 2, and 361 in Arm 3. For the primary comparison (Hyp 1.1) of Arm 1 (*n* = 180) versus the combined Arms 2 and 3 (*n* = 722), assuming ITT analysis with type 1 error probability of 0.05 (two-sided) yields 80% power to detect a small effect size of .23 SD for duration of feeding tube use. For the analysis of Hyp 1.2 in the gate-keeper approach, we will compare intensity of PRO-ACTIVE therapies (Arm 2 versus Arm 3, *n* = 361 per group), assuming type 1 error probability of 0.05 (two-sided), we have 80% power to detect again a small effect size of 0.21 SD for the primary endpoint of feeding tube duration. We expect the t-test will not be sufficient as the primary analysis given it does not allow for covariate adjustment. Therefore, we will apply the multiple linear regression model as the primary analysis for Aim 1. The power calculation conducted assuming t-tests for analysis of hypotheses 1.1 and 1.2 and deriving a sample of 952 patients remain sufficient for the linear model because by adjusting for variables associated with the mean response, the distribution of the residuals is expected to improve. Therefore, the power for the same hypothesized difference in the primary outcome attributed to treatment in the regression framework will be at least as much as for that for the t-test.

For the secondary analysis (Aim 2) in the gate-keeper approach, we will compare intensity of PRO-ACTIVE therapies (Arm 2 versus Arm 3, *n* = 361 per group), assuming type 1 error probability of 0.05 (two-sided), we have 80% power to detect again a small effect size of 0.24 SD for PROs and VFS measures. The attrition factor for the secondary analysis is set at 26% because they are more prone to attrition due to required clinical visits and survey responses required from participants. As an exception, feeding tube dependence at 3-months uses an attrition factor of 5%, for the same rationale as the primary endpoint.

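### The secondary ANCOVA adjusts only for each outcome's own baseline and omits site and the primary model's prognostic factors: a valid test that gives up modest precision

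*Protocol article*

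**What the plan says.** All references are to the protocol article.

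- **Secondary endpoints.** With a baseline, continuous outcomes are analysed by "multiple linear models regressing outcome on randomization arm plus the baseline measure for adjustment". Without one, the analysis is "a t-test (or suitable replacement) otherwise". No other covariate is named.
- **Primary endpoint.** The primary model has a fixed covariate list, which opens "The meaningful variables we will include in the regression model are: age (as a continuous variable); HPV status (oropharyngeal site vs all others" and goes on to surgery, chemotherapy, radiation dose and facility.
- **Overview of trial design.** "The randomization of participants will be stratified by participating site".
- **Secondary outcomes.** Dysphagia measured by the MDADI, itself a secondary outcome, is described as "time-dependent, radiotherapy dose-dependent and varies by extent of surgery and tumor site in HNC samples".
- **Sub-group analyses.** "Preliminary data suggest superior swallowing outcomes in younger patients". The sentence adds HPV-associated cancer, no prior surgery, lower dose, no chemotherapy and no prophylactic tube.
- **Sample size calculation.** Covariate adjustment in Aim 1 is justified because "by adjusting for variables associated with the mean response, the distribution of the residuals is expected to improve".
- **Missing data (end of the Primary endpoint section).** For outcomes missing in more than 10% of patients, inverse probability weighting and chained-equation imputation are named as possibilities. If inferences agree, the complete-case result is reported.

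**The concern.** The article's evidence that age, tumour type, surgery, dose and chemotherapy matter is largely evidence about swallowing outcomes. Yet the adjustment is made for tube duration and not for the swallowing measures themselves, and no reason is given. Site is also missing from the secondary model. When a stratification factor is prognostic, leaving it out of the analysis generally makes the standard error too large.

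The secondary outcomes already carry 26% planned attrition. They are also tested through a gate-keeper: pooled PRO-ACTIVE versus RE-ACTIVE comes first, and intensity is examined only if that succeeds. The first step has the smaller and less balanced comparison, so lost precision matters most there.

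**Working it through.** **Inputs.** Allocation 190 : 381 : 381, two-sided 0.05, 80% power, 26% attrition and 0.24 SD come from the Overview of trial design and the Sample size calculation. The share of variance explained by the omitted covariates beyond baseline (partial R²) is in neither section. It is assumed to be 0 to 0.20.

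**1. The plan's own figure.** The detectable effect is (1.960 + 0.842) × √(1/n₁ + 1/n₂). At 26% attrition, 381 × 0.74 ≈ 282 per arm, giving 2.802 × √(2/282) = 0.236, which rounds to the stated 0.24. Power at 0.24 SD is 81.3%. (The 361 per group printed beside 0.24 SD would give 0.209, so the figure rests on 282.)

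**2. The first gate-keeper step.** 190 × 0.74 ≈ 141 versus 564: 2.802 × √(1/141 + 1/564) = 0.264 SD. Power at 0.24 SD is 72.2%.

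**3. Adding the covariates.** Five terms plus 10 indicators for 11 sites make 15 degrees of freedom. The standard error is multiplied by √[(1 − R²)(N − 3)/(N − 18)], with N = 564 or 705. SD here means the SD left after baseline.

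| Partial R² | EAT v EAT+EXERCISE: detectable SD; power at 0.24 | Pooled PRO-ACTIVE v RE-ACTIVE: detectable SD; power at 0.24 |
|---|---|---|
| Baseline only | 0.236; 81.3% | 0.264; 72.2% |
| 0 | 0.239; 80.3% | 0.267; 71.3% |
| 0.05 | 0.233; 82.2% | 0.260; 73.5% |
| 0.10 | 0.227; 84.2% | 0.253; 75.7% |
| 0.20 | 0.214; 88.2% | 0.238; 80.5% |

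Expressed as sample size, 1/(factor²) − 1 is +2.4% and +3.0% at R² = 0.05, +21.7% and +22.3% at 0.20, and −2.7% and −2.1% at 0. Break-even is R² = 15/(N − 3): 15/561 = 2.7% and 15/702 = 2.1%.

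**4. Dropout.** A simulation used a true effect of 0, about 26% overall dropout, 1:4 allocation, and a standardised covariate index explaining about 5% or 10% of the variance. The dropout slopes are assumptions.

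- Dropout depends on the index equally in both arms: bias about 0.00 SD.
- Same slope, but 28% dropout in PRO-ACTIVE and 19% in RE-ACTIVE: 0.01 to 0.02 SD.
- Slope differs between arms: 0.03 to 0.09 SD.
- With the index in the model, the complete-case estimate stayed within 0.004 SD of zero in every scenario.

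**The case against.** Four points on the other side carry weight.

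- **Validity.** Under randomization, ANCOVA on arm and baseline is a valid analysis. A reader might infer that the secondary comparisons are biased or the tests wrong; the documents do not support that.
- **A reason for the difference.** Post-RT tube days have no baseline value of the same measure, so covariates are the main way to adjust the primary model. The argument in the Sample size calculation is made for Aim 1, against an unadjusted t-test. The two models are therefore not in contradiction. Even so, the article's statements on prognosis apply directly to the secondary measures, and a baseline score does not make the other factors redundant.
- **Power.** The only secondary target stated, 0.24 SD for EAT versus EAT+EXERCISE, is already met at 81.3%. The 72.2% applies that figure to a comparison for which the article sets no secondary target. This stands; 0.24 SD is only a yardstick there.
- **Missing data.** Weighting and imputation are foreseen. They are worded as options, name no covariates, and give way to the complete-case result when inferences agree, so some exposure remains.

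A reader might also infer that baseline scores explain little, because DIGEST grade 2 or above is excluded at entry. That is not shown. The article's correlations of DIGEST with MDADI (−0.41) and PSS-HN (−0.49) imply only about 17% and 24% shared variance, so restricting DIGEST need not compress those measures. For the CBI, four-month test-retest r = .890 (about 79% of variance) points the other way.

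**Conclusion.** The point holds as one of efficiency and consistency. The secondary model for continuous outcomes omits site and five factors that the plan itself treats as prognostic. For an assumed partial R² of 0.05 to 0.20, including them is worth about 2% to 22% more patients. Power at 0.24 SD rises by about 1 to 7 percentage points for the intensity comparison and 1 to 8 for the pooled comparison. The gain is cheap rather than free, because below a partial R² of about 2% to 3% it becomes a small loss.

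A reader might go further and infer that dropout related to these covariates by itself biases the complete-case comparison. It does not. Bias needs the dropout rate, or its relation to the covariates, to differ by arm. That is conceivable in a trial unblinded to participants, where therapy contact in the RE-ACTIVE arm depends on a trigger, but the documents do not show it. Protection against such bias is a secondary benefit, and its size rests on assumed slopes.

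**What to change.** In the Secondary endpoints section, define the model for continuous outcomes as arm, baseline value of the outcome where one exists, site, age, oropharyngeal site versus other, prior surgery, planned chemotherapy and planned radiation dose, all as known before randomization. This also replaces the unadjusted t-test for continuous outcomes without a baseline. In the missing-data paragraph, name the same variables for any weighting or imputation model.

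The cost is a few lines of text and 15 degrees of freedom. No new assessment should be needed: eligibility turns on planned dose, and the screening log records age, tumour and treatment plan. The primary model does not say whether its chemotherapy and dose terms are planned or delivered values, so the sponsor should confirm that the planned values are held in the trial database.

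### The secondary-outcome rule leaves 3-month feeding tube duration and feeding tube rates without the covariate and site adjustment used for 12-month duration, at a modest cost in precision

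*Protocol article*

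**What the plan says.** All references are to the protocol article.

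- **Outcomes.** Under Aims and hypotheses, "the second aim will compare the benefit on reduced duration of feeding tube presence at 3-month post radiotherapy". The same paragraph lists "diet level, feeding tube rates, weight loss, hospitalization" among the secondary outcomes.
- **12-month definition and model.** The Primary endpoint section defines duration as the "count of days of tube use from end of RT to last tube use within the 12-month study period" and disregards a tube that is in place but unused. The arms are compared "by means of a multiple linear regression model with covariate adjustment". The covariates are age, HPV status (coded as oropharyngeal v other site), surgery, chemotherapy, radiation dose and "facility (as a categorical variable to account for practice variation across the eleven sites".
- **Reason for that model.** The Sample size calculation section states: "We expect the t-test will not be sufficient as the primary analysis given it does not allow for covariate adjustment". It then adopts the regression for Aim 1.
- **Secondary rule, continuous outcomes.** The Secondary endpoints section uses a linear model on arm and the baseline measure "when a baseline measurement is present and a t-test (or suitable replacement) otherwise".
- **Secondary rule, binary outcomes.** "Binary outcomes will be compared by means of a chi-square test or Fisher’s exact test if expected counts are less than 5", with the effect given as a risk difference and 95% confidence interval.
- **Randomization.** The trial design overview states that allocation is stratified by participating site.

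**The concern.** A count of days that starts when radiotherapy ends cannot have a pre-radiotherapy value. Under the secondary rule, 3-month tube duration therefore goes to the t-test branch, and none of the six primary covariates follows it there. The stated reason for not relying on a t-test at 12 months is that it cannot adjust for covariates. That is a property of the test and applies equally at 3 months. Tube rates are also compared without adjustment, although baseline tube status is collected: the Tube PRO has a baseline entry in Table 1, and tubes in place at baseline are tracked.

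Both unadjusted tests also ignore the stratification by site.

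What is at stake is precision on the 3-month counterpart of the main endpoint. Under Hyp 2.2, EAT is compared with EAT+EXERCISE only for secondary outcomes on which PRO-ACTIVE is superior. Power lost in the first comparison therefore also lowers the chance of reaching the second.

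**Working it through.** **Inputs.** From the Sample size calculation section: two-sided alpha 0.05; 180 v 722 analysable patients at 0.23 SD for PRO-ACTIVE v RE-ACTIVE; 361 v 361 at 0.21 SD for the two PRO-ACTIVE arms. That section also gives the 3-month tube outcome the primary endpoint's 5% attrition, so the same numbers apply. From the Background: about 45% tube dependence 3 months after treatment. The R² of the covariates is not given, so it is assumed, with a range of 0.05 to 0.25.

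**1. The plan's own figures.** SE in SD units = √(1/180 + 1/722) = 0.0833.
- Effect detectable at 80% power: (1.960 + 0.842) × 0.0833 = 0.233 SD.
- Power at 0.23 SD: Φ(0.23/0.0833 − 1.960) = Φ(0.80) = 78.8%.
- EAT v EAT+EXERCISE: SE = √(2/361) = 0.0744; Φ(0.21/0.0744 − 1.960) = Φ(0.86) = 80.5%.

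Both agree with the stated 80% to within rounding. No printed figure is disputed here.

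**2. Effect of adjustment on power.** Adjustment multiplies the residual SD by √(1 − R²), so power = Φ(d / [SE × √(1 − R²)] − 1.960).

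| Assumed R² | 180 v 722, 0.23 SD | 361 v 361, 0.21 SD |
|---|---|---|
| 0 (t-test) | 79% | 81% |
| 0.05 | 81% | 83% |
| 0.10 | 83% | 84% |
| 0.15 | 85% | 86% |
| 0.25 | 89% | 90% |

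A noncentral t calculation for 180 v 722, with 15 covariate degrees of freedom (five single terms plus ten for eleven facilities), gives 80.8%, 82.8%, 84.9% and 89.0%. The covariates cost almost nothing in degrees of freedom.

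**3. Tube rates.** At 45% in both groups, the 95% half-width is 1.96 × √(0.45 × 0.55 × (1/180 + 1/722)) = 1.96 × 0.0414 = 8.1 percentage points. Multiplying by √(1 − R²) gives 7.9 (R² = 0.05), 7.7 (0.10) and 7.0 (0.25). The same variance-reduction factor is used here as an approximation for a standardized risk difference.

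**4. Ignoring the site strata.** If a share ρ of the outcome variance lies between sites and the arms are balanced within sites, the unadjusted test uses too large a standard error. Its true two-sided alpha is about 2 × [1 − Φ(1.96/√(1 − ρ))]: 0.048, 0.044 and 0.039 for assumed ρ of 2%, 5% and 10%. The test is conservative, not liberal. Facility is one of the covariates, so this is part of the R² in step 2 and not an additional loss.

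**The case against.** The strongest reply is that this is an ordinary hierarchy: a fuller model for the primary endpoint and simple, valid tests for secondary ones. Several parts of that reply stand.

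- **No formal contradiction.** A reader might infer that the plan rejects the t-test for this outcome and then uses it. The text does not support that. The t-test is called insufficient only as the primary analysis, and the regression is adopted for Aim 1. The reasoning carries over to 3 months; the statement itself does not.
- **No bias.** A reader might infer that a disagreement between the 3- and 12-month results could be produced by the method. In a randomized intention-to-treat comparison, the unadjusted and linear-model mean differences target the same average effect, as do the unadjusted and standardized risk differences. With about 900 patients they differ only through chance imbalance.
- **Not plainly the same quantity.** Aims and hypotheses speaks of tube presence at 3 months, the primary definition counts use, and the sample size section speaks of dependence at 3 months. The wording must be reconciled before the model is carried over. No version of the duration has a baseline value.
- **Not every binary outcome.** Nothing supports replacing the chi-square or Fisher test throughout. Some events may be rare, and an eleven-level facility term may not be estimable for them.
- **The covariates are not discarded from the trial.** They enter the primary model, and all but facility also appear among the subgroup analyses.

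Two replies do not remove the point. The allowance for a suitable replacement names neither a model nor covariates. The section's reference to a mean adjusted difference does not supply them either, since a t-test yields no adjusted difference. Nor is this simply detail left to an analysis plan: the article names the tests, and the tests it names are unadjusted.

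**Conclusion.** The point holds as a moderate efficiency matter, confined to 3-month tube duration and feeding tube rates. The planned tests are valid. They forgo adjustment for factors the protocol itself treats as prognostic, and for the randomization stratum.

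The size depends entirely on an R² that the documents do not report. At R² of 0.05 to 0.10 the gain is about 2 to 4 points of power and 0.2 to 0.4 points of half-width, which is small. At 0.25 it is about 10 points of power and 1.1 points of half-width, but nothing in the documents shows that the covariates explain that much, least of all for a binary tube status. The case for change is that the gain, though uncertain, costs very little and puts the 3- and 12-month duration analyses on the same footing.

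**What to change.** In the Secondary endpoints section:

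1. Analyse 3-month feeding tube duration with the linear regression and covariates of the Primary endpoint section, using planned or baseline values of those covariates.
2. Make the tube-presence wording under Aims and hypotheses agree with the tube-use definition in the Primary endpoint section.
3. For feeding tube rates, report a covariate- and site-adjusted risk difference with 95% confidence interval, for example from logistic regression with standardization, adding baseline tube status.
4. Keep the t-test and the chi-square or Fisher test for these outcomes as sensitivity analyses. Keep chi-square or Fisher as planned for other binary outcomes with few events.

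The cost is a few sentences and a little more programming, with no new data. The small downside is that the tube-rate model may need simplifying if events are sparse by site; the rule for doing so should be fixed in advance.
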